## Abstract

**Background:**

Many stroke survivors suffer from paresis of lower limb muscles, resulting in compensatory gait patterns characterised by asymmetries in spatial and temporal parameters and reduced walking capacity. Functional electrical stimulation has been used to improve walking capacity, but evidence is mostly limited to the orthotic effects of peroneal functional electrical stimulation in the chronic phase after stroke. The aim of this study is to investigate the therapeutic effects of up to 10 weeks of multi-channel functional electrical stimulation (MFES)-assisted gait training on the restoration of spatiotemporal gait symmetry and walking capacity in subacute stroke patients.

**Methods:**

In a proof-of-principle study with a randomised controlled design, 40 adult patients with walking deficits who are admitted for inpatient rehabilitation within 31 days since the onset of stroke are randomised to either MFES-assisted gait training or conventional gait training. Gait training is delivered in 30-minute sessions each workday for up to 10 weeks. The step length symmetry ratio is the primary outcome. Blinded assessors conduct outcome assessments at baseline, every 2 weeks during the intervention period, immediately post intervention and at 3-month follow-up.

**Discussion:**

This study aims to provide preliminary evidence for the feasibility and effectiveness of MFES-assisted gait rehabilitation early after stroke. Results will inform the design of a larger multi-centre trial.

**Trial registration:**

This trial is registered at the Netherlands Trial Register (number NTR4762, registered 28 August 2014)

**Electronic supplementary material:**

The online version of this article (doi:10.1186/s13063-016-1604-x) contains supplementary material, which is available to authorized users.

## Background

Regaining independent gait is considered one of the primary goals in stroke rehabilitation [1–3]. In the early phase after stroke, the musculature of the affected side is often paretic or even paralytic. As a consequence, compensatory gait patterns characterised by asymmetries in spatial and temporal parameters may arise that tend to be persistent, even in patients who show substantial restoration of paretic leg motor control, perhaps due to mechanisms related to ‘learned non-use’ as has been described for the upper extremity [4]. These compensatory gait patterns are less energy-efficient and may negatively affect balance control leading to an increased risk of falls and injury as well as to limitations in functional mobility [5–8]. Furthermore, they may cause secondary complications, such as muscle shortening and joint deformation [6]. Restoration of gait symmetry can be accomplished by motor relearning and neuroplasticity, for which highly intensive, repetitive and task-specific training is essential in the early rehabilitation phase after stroke [9, 10]. The use of functional electrical stimulation (FES) timed to the gait cycle in the early phase after stroke may improve gait symmetry by enhancing neuroplasticity, preventing secondary complications, and by supporting the acquisition of an adequate compensatory strategy. Although the orthotic effects of peroneal FES (PFES) have been established, the therapeutic effect of PFES in the subacute phase has been scarcely investigated [11–19]. Furthermore, PFES assists the ankle dorsiflexion movement only during the swing phase and early stance phase of gait and does not support the more proximal movements of the lower limb. Several studies have shown that strength and range of motion of the knee flexors and extensors are associated with gait performance [20–22]. Thus, multi-channel FES (MFES) of the distal and proximal parts of the lower limb may be more effective in normalising the gait pattern by compensating for thigh and dorsiflexor muscle weakness. There is preliminary evidence of a positive therapeutic effect of MFES in early stroke rehabilitation on balance control and mobility [23–25]. However, it remains unclear whether MFES is effective for the restoration of gait symmetry. Furthermore, it remains unclear whether it is feasible to implement MFES in functional gait training including pre-gait activities. Due to the limited evidence of MFES-assisted gait training during early stroke rehabilitation we designed a proof-of-principle study. The aim of this study is to examine the feasibility and preliminary efficacy of MFES-assisted gait training on gait symmetry and walking capacity in patients in the subacute phase after stroke during their inpatient rehabilitation. We hypothesise that MFES-assisted gait training for maximally 10 weeks in the early phase after stroke is feasible and improves the step length symmetry compared to conventional gait training. I﻿﻿n this paper we describe the protocol of our study according to the SPIRIT guidelin﻿es (Additional file 1).

## Methods

### Design

A prospective, assessor-blinded, single-centre, proof-of-principle study with a randomised controlled two-armed parallel design is being conducted. Forty participants with gait impairments in the subacute phase after stroke who are referred for inpatient rehabilitation are randomly assigned in a 1:1 ratio to either an intervention group, receiving MFES-assisted gait training, or a control group, receiving gait training as usual. The intervention period lasts 10 weeks or until discharge from inpatient rehabilitation, whichever is sooner. Outcomes will be assessed every 2 weeks during the 10-week intervention period as well as after a 3-month follow-up period (Fig. 1).

**Fig. 1 Fig1:**
[figure not shown]
Schedule of enrolment, interventions and assessments

### Ethics

The study protocol has been approved by the Medical Ethics Committee (MEC) of the Academic Medical Centre Amsterdam (protocol number NL50002.018.14). Any changes to the study protocol or study procedures will be reviewed and approved by the MEC and communicated to relevant parties. A Dutch rehabilitation centre (Merem Rehabilitation Centre De Trappenberg in Huizen) granted approval to include and train participants. The study has been registered at the Netherlands Trial Register (number NTR4762, registered 28 August 2014). Additional file 2 provides an overview of the trial registration data.

### Participants

Participants are recruited at the rehabilitation centre. All stroke survivors admitted for inpatient rehabilitation are screened for eligibility by their physiatrist. Inclusion criteria are: (1) a clinical diagnosis of stroke (diagnostic criteria according to the World Health Organization definition) [26]; (2) within 31 days since stroke onset; (3) age between 18 and 80 years; (4) indication for gait training (according to the treating physiatrist); (5) sufficient capacity to stand between parallel bars with or without physical assistance and able to walk with aids and physical assistance from one physical therapist (Functional Ambulation Categories [FAC] score ≥1); and (6) passive range of motion (PROM) upon ankle dorsiflexion ≥0° with full knee extension. Exclusion criteria are: (1) subarachnoid haemorrhage or stroke in the cerebellum or brain stem; (2) severe spasticity of the knee or ankle flexors or extensors (i.e., Modified Ashworth Scale [MAS] ≥ 3); (3) pre-existing lower limb deficits or any other medical co-morbidities that might significantly interfere with gait (indicated by a self-reported maximum walking distance <300 meter or walking duration <6 minutes walking pre stroke); (4) severe cognitive problems or aphasia leading to severely impaired comprehension of test instructions; (5) medical conditions that might lead to inability to comply with the study protocol (e.g., congestive heart failure, chemotherapy, uncontrolled epilepsy, pregnancy, depression or psychotic disorder, etc.); (6) demand-type cardiac pacemaker, defibrillator or electrical implant; (7) metallic implant at the affected lower limb; or (8) present or suspected cancerous lesion at the affected lower limb. Potentially eligible participants receive verbal and detailed written information (see Additional file 3) about the study and are invited to participate. In case of willingness to participate, an intake assessment is performed by a researcher who explains the purpose and procedures of the study and asks for informed consent. The following demographics are recorded for each participant: gender, date of birth, body length, body mass, type of stroke, location of stroke (left, right or both), hemiplegic side (left or right), date of stroke, neglect (tactile and visual present or not), relevant co-morbidities, medication and FAC. Furthermore, the following sensorimotor characteristics of both lower limbs are recorded for each participant: Motricity Index (muscle strength) [27], Brunnström Fugl-Meyer Assessment (motor selectivity) [28], and specific parts of the Erasmus Medical Centre Modified Nottingham Sensory Assessment (tactile and proprioceptive sensation) [29], MAS (muscle tone) [30, 31] and passive range of motion at the hip, knee and ankle (PROM). Strategies for patient retention include sending newsletters, accommodating their schedules when planning follow-up visits, sending reminders of upcoming visits, and providing transport support.

### Interventions

#### Control group

Participants in the control group will receive regular gait training by a physical therapist and/or movement therapist depending on their needs. Typically, per week, three to eight 30-minute sessions of gait-oriented physical therapy are given on five working days for 6 to 12 weeks. This ‘usual care’ may include individual gait training, gait training in groups, fitness training, sports, and hydrotherapy. Walking aids, orthoses, orthopaedic shoes and medication may all be used, but not lower limb FES. Participants will not be restricted in their activities. Therapists are instructed to document characteristics of the gait training (duration, frequency and content) for each participant in weekly logs.

#### Intervention group

Participants in the intervention group receive the same amount of gait-oriented physical therapy, but gait training is assisted by MFES. Per week, MFES is delivered during one 30-minute session on five working days up to 10 weeks. Physical therapists and movement therapists specifically trained in the use of MFES carry out the gait training. They are instructed to document characteristics of the gait training (duration, frequency, content and intensity of MFES) for each participant in weekly logs. During an initial adaptation period of 4 days, the duration of MFES is gradually increased from 15 minutes (day 1) to 30 minutes (day 4). Thereafter, participants receive 30-minute session of MFES-assisted gait training on each workday.

### Multi-channel functional electrical stimulation device

The MFES device used in this study (NESS L300^™^ Plus, Bioness, Valencia, CA, USA; CE 0473) delivers electrical pulses during gait to muscles in the affected leg to promote ankle dorsiflexion in combination with knee flexion or extension. The device consists of two cuffs (lower leg and thigh), a foot switch, and a wireless control unit that activates the system by radio frequency signals (Fig. 2). In each cuff two cotton electrodes and a stimulation unit are embedded. The electrodes of the lower leg cuff are located over the common peroneal nerve and the tibialis anterior muscle to elicit ankle dorsiflexion. The electrodes of the thigh cuff are positioned over the vastus medialis muscle to promote knee extension or over the biceps femoris brevis muscle to promote knee flexion. With this configuration, either paretic muscles can be stimulated or spastic muscles antagonised. Figure 3 illustrates some examples of positioning of the thigh cuff and timing of the upper leg stimulation expressed as percentage of the gait cycle [32]. Authorised clinicians are specially trained to fit and set the MFES device. They fit the device at baseline and evaluate the settings of the device every two-and-a-half weeks. A force-sensitive resistor in the foot switch detects the force under the foot. A dynamic gait-tracking algorithm is used to detect whether the foot is on the ground (e.g., initial contact) or in the air (e.g., heel off) by analysing the foot pressure. Average stance and swing phases are calculated by the system and data is transmitted by radio signals to the stimulation unit allowing for the synchronisation of the stimulation in accordance with the timing of gait events (gait mode). During the fitting process, the clinician sets the stimulation parameters (intensity level, phase duration, pulse rate, waveform and maximum duration of stimulation, ramp up, extension and ramp down) for the gait mode with a hand-held computer (personal digital assistant; PDA). The peroneal stimulation starts at ‘heel off’ and terminates at ‘heel contact’. Stimulation can be extended beyond heel contact to control the first rocker. The thigh stimulation – biceps femoris brevis or vastus muscles – can start and end once or twice at any segment in the gait cycle, which is determined by the clinician. Participants who cannot walk without personal assistance receive MFES treatment in the NESS L300^™^ Plus clinician mode (pre-gait and balance training) and gait mode (gait training) during individual physical therapy. The clinician mode is used to manually start and stop stimulation in the thigh and lower leg unit simultaneously. The clinician mode uses the stimulation parameters set for gait mode.

**Fig. 2 Fig2:**
[figure not shown]
The functional electrical stimulation device including two cuffs, a foot switch, and a control unit

**Fig. 3 Fig3:**
[figure not shown]
Examples of thigh cuff muscle activation during the gait cycle

### Outcome measures

#### Primary outcome

The primary outcome to determine efficacy of MFES-assisted gait training is the step length symmetry ratio. Step length during comfortable gait is measured with a spatiotemporal gait analysis system (SGAS) using a laterally placed camera (Panasonic HC-V550 High Definition camera 50 Hertz; Panasonic, Osaka, Japan) and discrete linear transform matrix software designed for this study. Participants walk at comfortable walking speed along a 10-metre walkway until three valid gait trials are collected in which each foot lands within the 1300-millimetre-wide video frame for both sides. The primary condition is walking without shoes and orthosis with minimal use of walking aids. The symmetry ratio is calculated as the difference between the step length of the affected and non-affected leg divided by the mean of the step length of both legs.

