#### Primary and secondary analysis

Primary efficacy analysis will be performed on an intention-to-treat basis. In addition, per protocol analyses will be performed. A linear mixed model for repeated measures will be used to analyse differences in the primary outcome and secondary outcomes. A squared time variable will be included to test for a curvilinear recovery curve. The interaction of time by intervention (MFES versus control) assesses whether the slopes of the recovery curves differ between groups. In these analyses both the intercept and the time variable are included as random effects. Group comparisons at the end of the intervention period for the three-dimensional gait analysis parameters and FES-I will be performed with Student’s *t* tests. To assess feasibility of the intervention, the proportion of participants in the intervention group who are compliant with the gait training and who scored ≥7 on the numeric rating scale will be determined. Patient satisfaction with the MFES device will be described. In all analyses, statistical uncertainty will be expressed by means of 95 % confidence intervals. Significance will be set at *p* < 0.05.

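### The primary outcome formula has no absolute value and no stated direction of improvement; read literally, opposite step length asymmetries cancel in the planned mixed model

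*Protocol article*

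**What the plan says.** The Background section of the protocol article states the efficacy hypothesis: MFES-assisted training "improves the step length symmetry compared to conventional gait training". The Primary outcome section names the measure: "The primary outcome to determine efficacy of MFES-assisted gait training is the step length symmetry ratio". It then gives the formula: "The symmetry ratio is calculated as the difference between the step length of the affected and non-affected leg". The denominator is the average of the two step lengths. The two legs are identified by side, not as longer and shorter. The section gives no absolute value, no order of subtraction, no target value and no direction of improvement.

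The section Primary and secondary analysis says: "A linear mixed model for repeated measures will be used to analyse differences in the primary outcome and secondary outcomes". The treatment effect is read from the slopes: "The interaction of time by intervention (MFES versus control) assesses whether the slopes of the recovery curves differ between groups". On the random part it says: "In these analyses both the intercept and the time variable are included as random effects". It does not mention rescoring the ratio before modelling.

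**The concern.** The hypothesis is about symmetry, and on this index symmetry is the value 0. If the index carries a sign, getting better means falling for a patient whose score is above 0 and rising for one whose score is below 0. The planned test compares mean slopes, and a mean slope adds the two kinds of improvement with opposite signs. A real benefit of MFES could then be diluted or lost in the only primary outcome. If an absolute value was meant, the formula does not say so, and two analysts could compute different primary outcomes from the same recordings.

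Nothing in the design removes the problem. The eligibility criteria do not restrict the direction of asymmetry. Randomisation is stratified only by walking dependence (FAC 1-2 versus 3-5).

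**Working it through.** **Inputs.** From the article: the formula (Primary outcome), the mixed model with a time-by-intervention effect and random intercept and slope (Primary and secondary analysis), and 20 participants per group (Sample size). The article gives no effect size, standard deviation or power, and no distribution of the direction of asymmetry, so there is no figure of the plan's own to reproduce. Every other number below is an assumption for illustration.

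**Step 1: the literal formula.** Write A for affected and N for non-affected step length. The index is I = (A - N) / ((A + N)/2).

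- A = 50 cm, N = 30 cm: I = 20/40 = +0.50.
- A = 30 cm, N = 50 cm: I = -20/40 = -0.50.
- Mean of the two: 0.00, which reads as perfect symmetry. Mean of the absolute values: 0.50.

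Reversing the order of subtraction flips every sign and leaves the cancellation as it is.

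**Step 2: crossing 0.** A patient who goes from +0.2 to -0.2 has a signed change of -0.4 and a change in the size of asymmetry of 0. The signed model counts this as steady progress in one direction.

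**Step 3: how much cancels.** Let c be the mean change in the size of asymmetry in a group, and q the share of patients with the minority direction. Assume that nobody crosses 0, and that direction is unrelated to the size of the change. The expected signed change, up to the choice of sign, is

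(1 - q) × c + q × (-c) = (1 - 2q) × c.

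With the same expected q in both arms, the group difference shrinks by 1 - 2q. Random intercepts and slopes do not alter this, because the tested effect is the difference in mean slopes.

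**Step 4: numbers.** Assume a mean starting asymmetry of 0.40, of which control removes 30% and MFES 60%. The true difference in change is 0.40 × (0.30 - 0.60) = -0.12.

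| q | 1 - 2q | Expected signed difference |
|---|---|---|
| 0 | 1.0 | -0.120 |
| 0.1 | 0.8 | -0.096 |
| 0.2 | 0.6 | -0.072 |
| 0.3 | 0.4 | -0.048 |
| 0.5 | 0.0 | 0.000 |

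**Step 5: the planned model.** A small simulation (60 runs per row) fitted time, time squared, group and time by group, with random intercept and slope. It used 20 per arm, visits every 2 weeks from week 0 to week 10, starting asymmetry with SD 0.15 and measurement SD 0.05. The table shows the mean time-by-group estimate and the share of runs with p < 0.05.

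| q | Signed index | Absolute value |
|---|---|---|
| 0 | -0.121 (98%) | -0.121 (97%) |
| 0.2 | -0.079 (38%) | -0.124 (100%) |
| 0.3 | -0.034 (10%) | -0.119 (98%) |
| 0.5 | +0.008 (8%) | -0.117 (93%) |

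The signed estimates follow the factor in Step 3 within the noise of 60 runs.

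**Step 6: sensitivity to the assumptions.** A simpler simulation used a t test on change, starting-asymmetry SD 0.16, measurement SD 0.08, and reductions of 30% and 60% that varied between patients with SD 0.25. On the signed scale, power was 58%, 32%, 18%, 9% and 5% at q = 0, 0.1, 0.2, 0.3 and 0.5. On the absolute scale it was 51-52% throughout. The power levels therefore depend heavily on assumed variability. The pattern across q does not.

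**The case against.** The strongest reply is that the article never says the difference is signed. The difference between two lengths can mean an unsigned difference, and an unsigned measure suits the stated aim better. The article also condenses a fuller protocol that may settle the scoring. This is right as far as it goes: a reader might infer that the trial definitely analyses affected minus non-affected, and the text does not establish that. The point still stands, because the article is not silent. It prints a formula for its primary outcome, names the legs by side, and omits the one element that would make the measure direction-free.

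Four further inferences go beyond the documents.

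- *The outcome cannot measure restoration of symmetry.* If all patients deviate the same way and none crosses 0, the signed and absolute forms agree in size. With noisier data the signed form was slightly more powerful at q = 0 (58% versus 52%).
- *The power figures describe this trial.* They do not. Size of asymmetry, variability, treatment effects and q are all assumed, and the study makes no power claim.
- *A chance imbalance in direction between arms produces false positives.* Allocation is random, so with no treatment effect such imbalance is sampling variation that the standard error reflects. What is shown is lost sensitivity.
- *The stance-time and swing/stance ratios share the defect.* Secondary outcomes lists them without formulas, so this can only be asked.

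It is also fair to say that the absolute value has costs of its own; these are set out with the change below.

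**Conclusion.** The concern holds as a defect in the stated definition. The formula does not say whether the sign is kept or that improvement means approaching 0. Read literally, it makes the planned slope comparison an unreliable test of the symmetry hypothesis. The expected group difference is multiplied by 1 - 2q, from no loss at q = 0 to complete loss at q = 0.5. That factor assumes no crossing of 0 and a direction unrelated to the size of change; crossing adds the separate problem that overshoot is scored as further change. Where the trial lies in this range cannot be determined from the article, and the simulated power figures are illustrative only. If an absolute value was always intended, the remedy is the same sentence and nothing is lost.

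**What to change.** In the Primary outcome section, state that the primary outcome is the absolute value of the step length index, that 0 means symmetric, and that lower is better. Fix the order of operations: average the signed index over the three valid trials at a visit, then take the absolute value, so that trial-to-trial noise is reduced before the sign is dropped. In the section Primary and secondary analysis, state that this value enters the mixed model, transformed if skewed. Report the signed index descriptively by group and visit, with the order of subtraction given, so that readers can see the mix of directions and any crossing of 0. Confirm that the stance-time and swing/stance ratios are also direction-free.

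The cost is a few sentences and a line of analysis code. The recordings already planned are sufficient, and enrolment was still under way when the article was submitted. There are three downsides:

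- The absolute value is right-skewed.
- It is biased slightly upward near 0. For a truly symmetric patient with normal measurement error of SD 0.05 (assumed), the expected value is 0.05 × √(2/π) = 0.05 × 0.80 = 0.04 instead of 0.
- It loses a little power if every patient deviates in the same direction: 52% versus 58% in the t-test simulation, 97% versus 98% in the mixed-model one.
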